**Methods/Design:**

The DiaCert-study is a two-arm, randomized controlled trial that will include 250 patients with diabetes type 2. At baseline, participants are randomized 1:1 to intervention, i.e. use of the smartphone-app, during 12 weeks, or to a control group receiving only standard care. Physical activity and sedentary behavior, is objectively measured using the Actigraph GT3X. Biomarkers including HbA1c and blood lipids are measured in fasting blood samples. Anthropometrics include height, weight, waist circumference and body composition, and a number of lifestyle factors including sleep, diet, self-efficacy, and quality of life, are assessed through an extensive questionnaire. Measurements are made at baseline and at follow-up after 3, 6 and 12 months.

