### Hypothesis

The hypothesis is that the smartphone-app intervention to promote daily physical activity will be effective in increasing physical activity, improving cardiovascular risk factors and other lifestyle factors after 12 weeks of active intervention and long term at 6 and 12 months of follow-up in the intervention group compared to the control group.

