## Methods

### Study design and recruitment

The DiaCert-study is a randomized controlled trial with two parallel arms. Patients fulfilling the inclusion criteria are recruited from five primary health care centers around Stockholm, Sweden. Each primary care center volunteered to participate in the study and data collection is performed in collaboration with clinicians and nurses at the centers. Patients that sign up for the study at the health care clinics are contacted by phone. During that contact, patients are given more information about the study. If they fulfill the inclusion criteria and agree to participate they are booked for a meeting in person at which they give their signed informed consent to participate, respond to a lifestyle questionnaire and have baseline measurements taken.

At baseline, study participants are randomized 1:1 to the intervention or control group. All participants, both in the intervention and the control group will continue to receive standard care, i.e. continue their usual care as prescribed by their primary care giver at each participating center, during the whole study period. For participants in the intervention group, the active intervention, i.e. use of the smartphone-app, last for 12 weeks from baseline. All study participants will meet with study personnel at baseline and are followed-up after the intervention at 3 and 6 months, and again after 1 year for assessment of clinical and life style factors. Physical activity is measured using the Actigraph GT3X at baseline and follow-up. For ethical reasons, participants in the control group are offered to use the smartphone-app at the 6-month follow-up if they want. Participants in the intervention group will be offered to download the app again at the same occasion if they wish to start using it again. The study design is outlined in Fig. 1.

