### Randomization and blinding

Study participants are randomized to either intervention group (standard care and use of the DiaCert smartphone-app) or control group (only standard care) at baseline at a 1:1 ratio by means of a random allocation sequence list generated in STATA 14.0. Women and men are randomized separately in blocks of ten within each participating primary health care center. Participants are, however, not blind to their allocation due to the nature of the intervention.

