#### Download

The intervention group will download the DiaCert smartphone-app which is connected to a digital platform where the care giver can follow the activity (daily steps) of each individual user. The app is demonstrated and downloaded at the introductory baseline meeting. An individual user account for each study participant is created by the study personnel on the digital platform where data is stored. Unique and temporary 6-digit codes are used to ensure a secure connection to the app for each participant. The individual access codes are created by study personnel and communicated to participants via telephone 7 days after the introductory meeting to avoid overlap with baseline accelerometer measurements. Daily steps measured by the smartphone are thereafter registered and displayed automatically in the app.

After 12 weeks of usage, participants in the intervention group are asked to remove the app from their phones and respond to a short questionnaire including 16 questions about using the app. At the 6-month follow-up, all participants (both in the intervention and control group) are offered to download and connect to the app.

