### Statistical analysis

Descriptive statistics will be used to describe characteristics of the study population at baseline. If differences in baseline characteristics are detected, potential confounders will be taken into consideration in further analysis. Data will also be checked for missing values, outliers and normality.

We will summarize pre-specified outcome measures assessed at 12 and 24 weeks of follow-up and compare intervention and control group assessing differences between groups using t-tests, ANOVAs and logistic regression. Analysis will be made following the intention-to-treat approach. Moreover, after completion of the study, follow-up assessment at week 52 will be analyzed within and between intervention and control groups to assess long-term effects. To assess the effect of both time and intervention on the outcomes, trends over time in outcomes will be analyzed using generalized estimation equations. Statistical interaction effects between characteristics and the intervention will also be tested for. Models will be adjusted for unbalanced baseline variables detected. We will also perform analysis stratified on age, sex, BMI, waist circumference, country of birth and primary health care center.

Additionally, results of usage and participants’ opinions regarding usability and satisfaction with the smartphone-app assessed using 16 questions asked at the 3-months follow-up, after the end of the active intervention, will be summarized in the intervention group and investigated in association to baseline factors, using linear and logistic regression.

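### At week 52 the randomised contrast is immediate versus delayed offer of the app, not app versus standard care, because both arms are offered the app at 6 months

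*Protocol article*

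**What the plan says.** The Hypothesis section of the protocol article expects the intervention to be effective at 12 weeks and also "long term at 6 and 12 months of follow-up in the intervention group compared to the control group". The Statistical analysis section carries this through to the last visit: "follow-up assessment at week 52 will be analyzed within and between intervention and control groups to assess long-term effects". The same section states that "Analysis will be made following the intention-to-treat approach" and adds generalised estimating equations for the joint effect of time and intervention on outcomes.

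The Study design and recruitment section says, giving ethical reasons, that "participants in the control group are offered to use the smartphone-app at the 6-month follow-up if they want". It continues: "Participants in the intervention group will be offered to download the app again at the same occasion". The Download section confirms that at 6 months "all participants (both in the intervention and control group) are offered to download and connect to the app".

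Neither the Statistical analysis section nor the limitations in the Discussion mentions this offer, says what the week-52 contrast then measures, or says how app use after month 6 is handled.

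**The concern.** The hypothesis asks whether the gain from a 12-week app intervention lasts, relative to patients who did not get the app. Answering that at 12 months needs a comparison arm that has not been given the app by then. By design the two arms have the same access to it from the 6-month visit onward. What still separates them by randomisation is that one arm was also offered the app at baseline.

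A week-52 result labelled as the long-term effect would be ambiguous in both directions. A small or null difference could mean that the early gain faded, or that controls caught up by using the app. A difference in favour of the intervention arm could reflect a lasting gain or renewed use after month 6. The month-12 term of a longitudinal model has the same ambiguity if it is read as an effect against standard care.

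The planned within-group analysis does not help. Change from baseline in one arm has no concurrent control, so it mixes any effect with time trends and regression to the mean. In the control arm it also spans six months in which the app was on offer.

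**Working it through.** **Inputs** (Sample size and power considerations): difference 8 min/day of moderate-to-vigorous activity, SD 20 min/day in both groups, 100 completers per group, two-sided 5%, 80% power, 20% dropout, 250 recruited.

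**1. The plan's own figure.** By the normal approximation, n per group = 2 × (1.96 + 0.842)² × (20/8)² = 98.1, rounded up to 99, or 198 in total. A two-sample t-test needs 99.1 per group. With 100 per group, t-test power is 80.4% (normal approximation 80.7%). Allowing for dropout, 200/(1 − 0.20) = 250. The stated sample size reproduces and is not in question.

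**2. What each arm is offered over time.**

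| Period | Intervention arm | Control arm |
|---|---|---|
| Baseline to 12 weeks | app + standard care | standard care |
| 12 weeks to 6 months | standard care, app removed | standard care |
| 6 to 12 months | standard care, app offered again | standard care, app offered |

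The first two rows support a comparison of app with standard care at 3 and 6 months. In the third row the offer is the same in both arms. The week-52 contrast is therefore immediate offer plus optional re-use against delayed offer.

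**3. How far this could move the contrast.** Uptake is not in the document, so this is a range and not a prediction. Let u be the share of controls who take up the app at month 6. Assume each of them gains the full 8 min/day and the intervention arm keeps its full 8 min/day. Then difference = 8 × (1 − u). Power is from a two-sided t-test with 100 per group and SD 20:

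| u | Difference (min/day) | Power |
|---|---|---|
| 0% | 8.0 | 80% |
| 10% | 7.2 | 72% |
| 25% | 6.0 | 56% |
| 50% | 4.0 | 29% |
| 75% | 2.0 | 11% |
| 100% | 0 | no difference to detect |

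**4. Sensitivity to the retention assumption.** Suppose intervention-arm participants without the app keep only half their gain, and both arms take up the app at the same rate u, with users in either arm at 8 min/day. Then difference = [8u + 4(1 − u)] − 8u = 4(1 − u). With u = 25% this is 3.0 min/day (power 18%); with u = 50% it is 2.0 (11%). With nobody using the app after month 6, the lasting effect under the same assumption would be 4.0. The observed contrast would thus understate persistence, by an amount that depends on unreported uptake.

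**5. The 6-month time point.** The accelerometer is worn for seven days (Physical activity section) and the app is offered at the 6-month visit. The Download section states a 7-day delay before access codes are given, but only for baseline. The 6-month comparison is clean only if that week of wear ends before the app is connected.

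**The case against.** Several objections carry weight.

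- **The comparison remains randomised.** The offer is optional, and controls who decline stay on standard care. Analysed by intention to treat, week 52 validly compares two strategies. A reader might infer that it is invalid or uninformative. The documents do not support that: only its reading as app versus standard care fails.
- **The control definition is not clearly contradicted.** A reader might set the abstract's "or to a control group receiving only standard care" and the randomisation section's "control group (only standard care) at baseline at a 1:1 ratio" against the month-6 offer. But the abstract contrasts this with app use over 12 weeks, and the other sentence describes allocation at baseline. Neither says that controls stay without the app for a year, and the offer is openly disclosed. The conflict lies between the hypothesis and week-52 analysis on one side and the offer on the other.
- **The dilution figures rest on assumptions.** Uptake could be low. The active intervention included a goal review by study personnel every two weeks, and the text does not say that this accompanies the month-6 offer. A full 8 min/day per control user may therefore be generous. This stands.
- **A restart effect needs unequal use.** Both arms get the offer at the same visit, and nothing in the document says that the intervention arm would use the app more. Inflation of the contrast is possible but not shown.
- **Week 52 is not the main comparison.** The main aim concerns a 12-week intervention, and the analysis section puts weeks 12 and 24 first. This lowers the severity.
- **A full analysis plan might deal with post-6-month use.** It could report or model that use. It could not restore a concurrent arm that had not been offered the app, and the 12-month hypothesis and its planned comparison are stated in the article itself.

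**Conclusion.** The point holds for the label and interpretation of week 52. As written, the plan presents an immediate-versus-delayed-offer contrast as the long-term effect against the control group, and the design does not support a 12-month conclusion about app versus standard care.

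The size of the effect on the contrast is unknown because uptake is not given. Under the stated assumptions (full retention in the intervention arm, 8 min/day per control user, 100 per arm, SD 20), control uptake of 25% to 75% leaves 6 to 2 min/day and 56% to 11% power, against 80% with no uptake. A reader should not take any one of these as the expected loss.

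The 3-month comparison is unaffected. So is the 6-month one, provided its measurements are complete before the app is connected. This should be fixed, but it does not threaten the trial's main comparison.

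**What to change.** 1. Limit the hypothesis of app versus standard care to 3 and 6 months.
2. State that all 6-month measurements, including the seven days of accelerometer wear, are completed before the app is connected in either arm.
3. Keep the randomised intention-to-treat comparison at week 52, tested if wished, but call it immediate versus delayed offer of the app. Give any month-12 term in the longitudinal model the same label.
4. Report app connection in months 6 to 12 by arm. The digital platform holds individual accounts and daily steps, so no new data collection should be needed.
5. Say that within-group change at week 52 is not evidence of a long-term effect.

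The offer to participants need not change. The cost is revised wording in the Hypothesis and Statistical analysis sections, one table of app use, and a check on the timing of connection at 6 months. The wording should be settled before week-52 results are seen. What is given up is a 12-month claim against standard care that the design does not support.

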### Sample size and power considerations

Power calculations were performed prior to study start to ensure sufficient power to detect a clinically significant difference in the primary outcome (accelerometer measured physical activity). A total of 200 patients (100 in each group) completing the study would provide sufficient statistical power (80%) at the two-sided 5% significance level to detect a difference in moderate-to-vigorous activity of 8 min/day (e.g. 22 min/day vs. 30 min/day). A standard deviation of ±20 min/day of moderate-to-vigorous activity was assumed in both groups. To cover for a 20% dropout rate (based on earlier intervention studies conducted by our research group), we will recruit 250 patients (125 in each group) to the trial.

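### The week-52 between-arm comparison contrasts an early with a delayed offer of the app, not the 12-week course with standard care alone, because both arms are offered the app at month 6

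*Protocol article*

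**What the plan says.** All statements are in the protocol article.

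- **Hypothesis:** the app is expected to be effective after the 12 active weeks and "long term at 6 and 12 months of follow-up in the intervention group compared to the control group".
- **Randomization and blinding:** the comparator is a "control group (only standard care").
- **Study design and recruitment:** for ethical reasons, "participants in the control group are offered to use the smartphone-app at the 6-month follow-up if they want". Intervention participants are offered a new download at the same visit.
- **Download:** intervention participants are asked to remove the app after 12 weeks. At the 6-month visit, "all participants (both in the intervention and control group) are offered to download and connect to the app".
- **Statistical analysis:** groups are compared at 12 and 24 weeks by intention to treat. After that, "follow-up assessment at week 52 will be analyzed within and between intervention and control groups to assess long-term effects".

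The analysis text does not describe week 52 as a comparison of early with delayed access, and the Discussion does not list the month-6 offer among the limitations.

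**The concern.** The 12-month hypothesis needs a control arm that has had standard care only. The design secures that arm up to the 6-month visit and then makes the app available to everyone. From then on the randomised difference between the arms is whether the app was also offered at baseline. Later use is self-selected in both arms.

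If the plan is followed as written, the week-52 difference will be reported as the long-term effect against control. A small or null difference could mean that the benefit faded, or that it lasted and controls caught up, and the planned comparison cannot tell these apart. Physical activity, the primary outcome, is among the outcomes covered by the hypothesis.

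**Working it through.** **1. The plan's own figure.** Sample size and power considerations sets the calculation "at the two-sided 5% significance level to detect a difference in moderate-to-vigorous activity of 8 min/day", with 100 completers per arm and 80% power. On variability: "A standard deviation of ±20 min/day of moderate-to-vigorous activity was assumed in both groups".

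- n per arm = 2 × 20² × (1.960 + 0.842)² / 8² = 98.1, rounded up to 99; the plan uses 100.
- Two-sample t-test, 100 per arm: noncentrality = 8 / (20 × √(2/100)) = 2.83, power 80.4%.
- Allowance for 20% dropout: 200 / 0.8 = 250.

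The stated sample size reproduces and is not in dispute.

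**2. Expected difference at week 52.** The document gives none of these three quantities, so they are assumptions:

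- p = proportion of controls using the app after month 6
- q = proportion of the intervention arm re-using it
- r = share of the 8 min/day that persists without the app

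Assume also that every later user is at the full 8 min/day at month 12. Then:

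- intervention arm gain = 8 × [q + (1 − q) × r]
- control arm gain = 8 × p
- difference with the offer = 8 × [r + (1 − r) × q − p]
- difference without the offer = 8 × r

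The offer therefore changes the difference by 8 × [(1 − r) × q − p].

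**3. Full persistence (r = 1).** The difference is 8 × (1 − p), whatever q is.

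| Control uptake p | Expected difference (min/day) | Power, 100 per arm, SD 20 |
|---|---|---|
| 0% | 8.0 | 80.4% |
| 10% | 7.2 | 71.7% |
| 30% | 5.6 | 50.4% |
| 50% | 4.0 | 29.1% |
| 70% | 2.4 | 13.5% |

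**4. Half persistence (r = 0.5).** The difference is 4 + 4q − 8p, against 4 without the offer.

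- p = q = 50%: 4 + 2 − 4 = 2 min/day, half the value without the offer.
- p = 20%, q = 60%: 4 + 2.4 − 1.6 = 4.8 min/day, more than without the offer.
- In general the difference exceeds 4 whenever q > 2p.

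**5. No persistence (r = 0).** The difference is 8 × (q − p). With equal uptake it is zero. It is also zero without the offer, because the intervention arm removes the app after 12 weeks. Here a null result is the right answer about persistence.

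**6. Is month 6 a clean comparison?** The accelerometer is worn for seven days and mailed back (Physical activity section). At baseline, access codes are held back seven days so that app use does not overlap with the measurement (Download section). No such hold is stated for month 6, where the offer is made at the follow-up visit itself.

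**The case against.** The strongest case on the other side has five parts.

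- **The offer is optional and uptake is unknown.** A reader might infer that week 52 cannot test the 12-month hypothesis at all. The document does not support that: at 10% uptake, 7.2 of the 8 min/day remains. This stands.
- **The direction is not fixed.** A reader might infer that the comparison is necessarily biased toward no difference. Shrinkage is expected if the effect persists and controls take up the app, but step 4 shows that re-use well above control uptake pushes the other way. This stands. So does the point in step 5: an app that works only while in use gives no persistence effect at 12 months with or without the offer, so that case is no evidence of bias.
- **The table leans to the unfavourable side.** The trial period has goal setting with study personnel and contact every two weeks; at month 6 the article mentions only an offer to download and connect. Late users may gain less than 8 min/day. This stands, so the table is a range under stated assumptions and not a forecast.
- **Week 52 remains a valid randomised comparison.** It does, for early versus delayed offer, and need not be discarded. That is still a different question from the one in the Hypothesis section.
- **Week 52 is secondary, and an analysis plan may deal with later app use.** The 12- and 24-week comparisons do come first. But the hypothesis, the month-6 offer and the stated purpose of week 52 are all in the article and conflict there. An analysis plan could refine the method; it would not change the hypothesis as published.

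**Conclusion.** The point holds as a mismatch between claim and comparison. Intention to treat at week 52 estimates the effect of offering the app at baseline and again at month 6, against first offering it at month 6. The Hypothesis and Statistical analysis sections present it as long-term effect against control.

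Under full persistence and full benefit to control users, uptake of 10% to 70% takes the expected difference from 7.2 to 2.4 min/day and power from 71.7% to 13.5%. Under other assumptions the loss is smaller, absent or reversed. Because uptake and re-use are left to participants, what week 52 measures is not fixed by the design. The within-arm change at week 52 is also mixed with re-use or first use of the app.

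The 3-month comparison and the stated sample size are unaffected. The 6-month comparison against standard care is sound if its measurements are complete before the app is activated, which the article does not say for the accelerometer week.

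**What to change.** Keep the month-6 offer and change the claim around it.

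1. **Hypothesis:** limit the between-arm long-term hypothesis against standard care to month 6. State that the 6-month accelerometer week is completed before app access is activated, as is already done at baseline.
2. **Statistical analysis:** label the week-52 between-arm result as early versus delayed offer of the app, and say that a null result will not be read as loss of effect.
3. **Reporting:** give, by arm, the number who connected to the app after month 6 and how long they used it. Interpret the between-arm and within-arm week-52 results alongside these figures. The article describes user accounts on the digital platform as part of the intervention-arm download, so confirm that the same records will exist for controls who connect later.

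Cost: the trial gives up its 12-month claim against standard care and needs a short delay in activating the app at month 6. The rest is rewording and one tabulation.
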